### Measurements

The potential effect of the DA will be evaluated by testing the improvements on the primary outcome for our study level of decisional conflict. Level of decisional conflict will be measured with the Decision Conflict Scale [55] that assesses patients’ perceptions of uncertainty, modifiable factors contributing to uncertainty, and ultimate satisfaction with the choice. It is one of the most robust and validated instruments to test the impact of DAs in end-of-life decision making [56]; We assume that the Decisional Conflict Scale score will decrease for the patients who use the DA.

Furthermore, we aim to assess the patients’ involvement in decision making, certainty about choice, and satisfaction with the oncologist-patient interaction as exploratory endpoints. Patients’ involvement in decision making will be assessed with the German questionnaire on shared decision making (PEF-FB-9) [57]. The trade-off between patients’ preferences for quality and length of life will be assessed with the validated German version of the Quality-Quantity Questionnaire [1]. The preferred role of the patient in decision making will be assessed with the German version of the Control Preference Scale [58]. Satisfaction with the oncologist-patient interaction will be assessed using the validated Questionnaire on the Quality of Physician-Patient Interaction (QQPPI) [59]. Effect on hope (German version of the Herth Hope Index [60]), anxiety (EQ-5D-5L [61]), quality of life (EORTC QLQ-C30 [62]), and documentation of patient preferences will be measured.

Description of the measures and their psychometric properties, scoring, and interpretation are provided in Table 1.

Such determinants of quality of palliative care as time of integration of specialized palliative services into care, aggressiveness of therapy (anticancer treatment <14 days before death), and place of death will be recorded.

During data collection, patients might have changes in mental status (ie, develop depression or cognitive problems) as well as experience changes in decision making. The study physician involved with data collection will document all possibly relevant factors.

The questionnaires will be completed by patients and oncologists before and after the intervention and will take approximately 15-20 minutes to complete. All assessments will be conducted in German.

**Table 1 table1:** Description of the measures and their psychometric properties, scoring, and interpretation.

Outcome	Instrument	Scoring and interpretation
Level of decisional conflict	Decision Conflict Scale	The German version of the Decision Conflict Scale demonstrated good psychometric properties. The internal consistency was found to be high (Cronbach=.96). It has 5 subscales with a total of 16 items and 5 response categories, ranging from 0 (strongly agree) to 4 (strongly disagree). The total score is calculated in the following way: The 16 Items are (1) summed, (2) divided by 16, and (3) multiplied by 25. Scores range from 0, no decisional conflict, to 100, extremely high decisional conflict.
Patients' involvement in decision making	Questionnaire for participatory decision making (PEF-FB-9)	The German questionnaire on shared decision making “Der Fragebogen zur Partizipativen Entscheidungsfindung” (PEF-FB-9) demonstrated high internal consistency (Cronbach=.93). It has 9 items scored on a 6-point Likert scale, ranging from 0 (not at all) to 6 (fully correct). The score is created by adding all items (range 0-45 points). A higher score means more shared decision making.
Trade-off between patients' preferences for quality and length of life	Quality-Quantity Questionnaire	The validated German version of the Quality-Quantity Questionnaire consists of 9 items in 2 preference dimensions: Q(uality) of life (QL) and L(ength) of life (LL). The scales demonstrated good and acceptable internal consistency (Cronbach=0.71 for LL and .59 for QL). Patients indicate how strongly they agree or disagree with the statements on a 5-point Likert scale. High scores on the quantity or quality scale indicate the importance of the length or quality of life, respectively.
Preferred role of the patient in decision making	Control Preference Scale (CPS)	The preferred role of the patient in decision making will be assessed with the German version of the CPS. It is a valid and reliable measure of preferred roles in medical decision making. It consists of 5 statements (A, B, C, D, E) that each portrays a different role in treatment decision making. For analysis, a categorical variable, which is the person's most preferred role in treatment decision making, will be created. Preference orders will be reclassified into Active (A, B), Collaborative (C), and Passive (D, E).
Satisfaction with the oncologist-patient interaction	Quality of Physician-Patient Interaction (QQPPI)	The German version of the validated QQPPI — “Fragebogen zur Arzt-Patienten-Interaktion” (FAPI) — showed very good reliability (Cronbach=.97). It has 14 items rated on a 5-point scale (range: 1 [I do not agree] to 5 [I fully agree]). The total score is calculated as a mean of all 14 items. The lowest score (1) indicates the lowest quality of physician-patient interaction, and the highest (14) indicates the highest quality of physician-patient interaction.
Effect on hope	German version of the Herth Hope Index (HHI-D)	The HHI-D has satisfactory reliability (Cronbach=.82). It has 12 items rated on a 4-point Likert scale that ranges from 1 (strongly disagree) to 4 (strongly agree), with items #3 and #6 reverse-coded. The scale has 1 global score that ranges from 12 to 48. Higher scores indicate more hope.
Effect on patients' quality of life	EORTC QLQ-C30	The EORTC QLQ-C30 questionnaire is widely used to measure the quality of life of cancer patients. The QLQ-C30 has a global health status scale, 5 functional scales, and 3 symptom scales. High scores on the functional scales mean healthy functioning. A high score for global health status means a higher quality of life. A high score on the symptom scales indicates a high level of problems. Scores for all scales and single items range from 0 to 100. The questionnaires will be interpreted following the official guidelines of the EORTC.
Effect on patients’ anxiety	Anxiety EQ-5D-5L	The EQ-5D-5L, a preference-based measure of general health status, consists of 5 dimensions (mobility, self-care, usual activities, pain/discomfort, and anxiety/depression), each with 5 levels of problems: 1=no, 2=slight, 3=moderate, 4=severe, and 5=extreme or unable to perform the task. The anxiety/depression dimension of the EQ-5D-5L will be used to detect anxiety and depressive symptoms.

### User Acceptance Testing With Oncologists and Patients

A variety of factors can affect users’ acceptance of a DA. Among these factors, users’ perceptions and expectations are the key factors that influence their acceptance. Therefore, we aim to survey the oncologists’ and patients’ acceptance of the DA. The acceptance testing will be conducted during the intervention phase with patients and oncologists who will be caring for the patients in the pre-post study. The major aim is to assess oncologists’ perceptions of the usefulness (how useful oncologists find the DA), willingness to use the DA in daily routine with patients (how comfortable they would be to use the DA with patients), willingness or readiness to use it in clinical practice (how likely they would use it within the next 5 months), and perceived need for the DA. In addition, the patients’ perceptions of usefulness and willingness to use the DA during consultations with their oncologists will be assessed. The oncologists who were involved in the development of DA will be excluded from acceptance testing.

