### Field Testing

In the field-testing phase, the feasibility of the DA will be evaluated in “real-world” settings by 16-20 patients and 4-6 oncologists who were not involved in the design phase. Feasibility is operationalized in terms of (1) time required for use and (2) acceptability for patients and oncologists. We will conduct qualitative interviews with patients and oncologists using the following questions:

What is the best time to use this DA?What is the best way to use the DA by oncologists and patients?Was the DA helpful to make a treatment decision?What did you find good about the DA?How do you think the DA could be improved?What impact did the DA have on the length of the consultation?Would you recommend using this DA? (patients); When would you use the DA in the future? (oncologists)

Each interview will last approximately 20-30 minutes. Qualitative data will be thematically analyzed. The analysis will be conducted analogous to the qualitative analyses described in the qualitative interviews and focus groups.

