### Measurements

In order to access oncologists’ acceptance of the DA, we plan to use the German version of the Ottawa Acceptability of Decision Rules Instrument (OADRI) [63]. It is a 12-item instrument developed to measure the acceptability of and willingness to use clinical decision rules in the future [64].

Patients’ acceptability will be measured with a question (whether the patient found the DA useful for their decisions) from the DA feedback questionnaire developed by Juraskova et al [65]. Our research team will translate it into German. We refrain from using long questionnaires for patients as they already have to fulfill the set of questionnaires from the pre-post design study.

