### Data Analysis

Analyses will be performed using SPSS v.20.0. A descriptive analysis of the sample will be performed. According to the level of variables, means, SDs, medians, minimum and maximum, and absolute or relative frequencies will be reported.

Clinically significant decisional conflict will be calculated and defined by a score of ≥25/100 on the Decision Conflict Scale, which is the most commonly used threshold to distinguish a harmful level of decisional conflict [62-64].

We will compare primary and exploratory outcome measures between the 2 patient groups (baseline and intervention) using Student *t* tests or analysis of variance. Parametric or nonparametric statistics (depending on the distribution of the data) will be used for the analysis of the patient groups from the baseline and intervention phases.

We will compare clinical confounders (time of integration of specialized palliative services into care; aggressiveness of therapy [anticancer treatment <14 days before death and place of death]) between the 2 patient groups (baseline and intervention) by comparing mean values. Measures of variability (SD) will be calculated.

Given the practice-based character and the small sample size of the study, we refrain from extensive measurement and multivariate analysis of mediators and moderators of the intervention effects. For the latter reason, we do not plan to use multiple imputation of missing values. Missing values will be handled by allowing a maximum of 35% missing in the calculation of scale scores.

*P* values of the corresponding statistical tests comparing treatment groups (ie, 2-sample *t* tests for continuous variables and chi-square tests for categorical data) will be given. Statistical significance will be assessed at the level of α=.05 (two-sided).

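### Patient willingness to use the decision aid is to be assessed, but the only patient acceptance question asks about usefulness

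*Protocol article*

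**What the plan says.** The relevant text is in two consecutive sections of the protocol article.

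User Acceptance Testing With Oncologists and Patients sets the aim. It places the work in the evaluation phase: "The acceptance testing will be conducted during the intervention phase with patients and oncologists who will be caring for the patients in the pre-post study". For oncologists it lists four constructs: usefulness, willingness in daily routine, readiness to use the aid in practice within the next 5 months, and perceived need. For patients it adds that "patients’ perceptions of usefulness and willingness to use the DA during consultations with their oncologists will be assessed".

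The Measurements section that follows names the instruments. Oncologists receive the Ottawa Acceptability of Decision Rules Instrument, described thus: "It is a 12-item instrument developed to measure the acceptability of and willingness to use clinical decision rules in the future". For patients the text reads: "Patients’ acceptability will be measured with a question (whether the patient found the DA useful for their decisions) from the DA feedback questionnaire". The reason given for stopping there is burden: "We refrain from using long questionnaires for patients as they already have to fulfill the set of questionnaires from the pre-post design study".

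**The concern.** The aim names two things to be learned from patients, and the measurement section provides for one. Usefulness and willingness can diverge. A patient may find the aid helpful in retrospect and still not want to work through it in a consultation about forgoing cancer-specific therapy, or may be willing to use it and find that it added little.

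If only usefulness is collected, a report on patient acceptance will either be silent on willingness, although the protocol promised it, or will let the usefulness answer stand for both. The data would also be hard to recover later, because the protocol describes these patients as near the end of life. What is not asked during the intervention phase is unlikely to be obtained afterwards.

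**Working it through.** No formula applies, and the plan states no figure to reproduce. The check matches each patient acceptance construct to the instruments that the protocol assigns to patients.

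**Step 1: constructs promised.** User Acceptance Testing names two for patients: (a) perceived usefulness and (b) willingness to use the aid during consultations. The same section lists usefulness and willingness separately for oncologists, so the authors do not treat the two as synonyms.

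**Step 2: the patient acceptance measure.** The Measurements section under acceptance testing gives one question, and its content is usefulness for the decision. It covers (a) and not (b).

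**Step 3: other patient measures in the pre-post study.** These come from the Measurements section of the pre-post study and its Table 1.

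| Patient instrument | What it captures, as described | Willingness to use the aid? |
|---|---|---|
| Decision Conflict Scale | Uncertainty, its modifiable causes, satisfaction with the choice | No |
| PEF-FB-9 | Involvement in decision making | No |
| Quality-Quantity Questionnaire | Trade-off between quality and length of life | No |
| Control Preference Scale | Preferred role in decision making | No |
| QQPPI | Quality of the physician-patient interaction | No |
| Herth Hope Index | Hope | No |
| EORTC QLQ-C30 | Quality of life | No |
| EQ-5D-5L | General health status; the anxiety/depression dimension is used | No |

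The Control Preference Scale comes nearest, but a preferred decision role is not readiness to use a particular tool.

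**Step 4: sources outside these instruments.** The Ottawa instrument covers willingness but is assigned to oncologists. The field-testing interviews ask patients whether they would recommend the aid. Those interviews belong to an earlier qualitative phase with 16-20 patients, before the final revision of the aid, and are not part of the acceptance testing.

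**Result.** Two patient constructs are stated and one item is specified: usefulness has 1 item, willingness has 0. Design and Settings plans 40 intervention encounters. Whatever number is reached, the item count is the same for every patient, so willingness is unobserved in all of them.

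**The case against.** The strongest reply is that this is one over-inclusive phrase and not a poorly chosen measure. Decisional conflict is the primary outcome, and willingness is not among the exploratory endpoints listed with it. In the acceptance section the oncologists' views are the major aim, and the patient sentence is an addition. The single question is a disclosed choice to spare very ill patients. Related evidence is also planned: recruitment and retention, documented drop-out reasons, and the field-testing interviews.

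Most of this stands as a limit on weight, but it does not close the gap. The protocol does not define recruitment, retention or drop-out as measures of acceptance, and the field-testing sample and phase are different. The burden argument explains why the patient measure is short; it does not explain why the aim names a construct that the measure omits.

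Nor is this a detail that a condensed article leaves to a fuller document. The article states the number of patient items and their content, and that statement conflicts with the stated aim. The source feedback questionnaire is not reproduced, so its exact wording and response options cannot be checked, but the article does say that the chosen question is about usefulness.

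A reader might also object that only patients who have used the aid are asked. That is not a defect: acceptance testing is placed in the intervention phase, and a question on whether the aid was useful has to follow its use.

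**Conclusion.** The inconsistency is real and small. The protocol commits to assessing patient willingness to use the aid, and no patient instrument in the pre-post study supplies the data. The primary outcome and its comparison between phases are unaffected; what suffers is a secondary, exploratory aim. It is worth correcting because acceptance is a stated purpose of this pilot and the correction is cheap.

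Three stronger readings are tempting and not supported:

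- **A trial endpoint has been lost.** The protocol says willingness will be assessed; it does not call it an endpoint.
- **A headline aim fails.** Acceptance is a genuine aim, but the abstract introduces it after the primary outcome, and patient willingness is one component of it.
- **Half of the patient acceptance information is missing.** One of two is a count of named constructs, not a measure of information.

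The conclusion rests on the instruments as the article describes them, and assumes that no willingness item is added to the single patient question.

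**What to change.** Preferred: add one short item to the patient questions in the intervention phase. It should ask directly whether the patient is willing to use the decision aid in a consultation with the oncologist, have a fixed response scale, and be reported separately from the usefulness question. The cost is one more item for patients who already complete a set of questionnaires, which remains compatible with the stated wish to avoid long ones.

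Alternative: delete willingness from the patient sentence in User Acceptance Testing and limit the patient acceptance conclusion to perceived usefulness. This costs one sentence and adds no burden, but gives up the question.

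The field-testing question on recommending the aid should not be reused for this purpose. Recommending a tool is a different construct from being willing to use it oneself in a consultation, so willingness would remain unmeasured.

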### Measurements

In order to access oncologists’ acceptance of the DA, we plan to use the German version of the Ottawa Acceptability of Decision Rules Instrument (OADRI) [63]. It is a 12-item instrument developed to measure the acceptability of and willingness to use clinical decision rules in the future [64].

Patients’ acceptability will be measured with a question (whether the patient found the DA useful for their decisions) from the DA feedback questionnaire developed by Juraskova et al [65]. Our research team will translate it into German. We refrain from using long questionnaires for patients as they already have to fulfill the set of questionnaires from the pre-post design study.

### Sample Characteristics

Patients will be recruited at participating study sites (Jena, Heidelberg) in inpatient and outpatient settings. Patients will be identified by a study nurse via the electronic health record of patients scheduled in the outpatient or inpatient clinic and approached for participation if they fulfill the inclusion criteria.

We will include adult patients with incurable, stage IV disease (prostate, breast, pancreatic, stomach, or colorectal cancer) in an advanced treatment stage (prognosis <12 months or standard palliative care only is considered). The patient must have an adequate level of the German language to complete the questionnaire and is willing and able to give informed consent for participation in the study.

We will exclude patients from the study who are already under standard palliative care only, are cognitively impaired, have extreme anxiety or distress, or have a severe comorbid illness, excluding antitumor treatment as assessed by the treating oncologist.

The influence of implicit bias will be reduced by recruitment of patients both in Heidelberg and Jena. In addition, the use of a trained study nurse at both sites will reduce implicit bias in recruitment. Drop-out reasons will be documented.

Oncologists will be recruited from the participating study sites (Jena, Heidelberg). They will be identified by a study nurse and invited to participate in the study via phone. We will include oncologists with different levels of working experience and of varying ages. The oncologists who participated in the development of the DA will be excluded from participation in the study.

### Data Analysis

Analyses will be performed using SPSS v.20.0. A descriptive analysis of the sample will be performed. According to the level of variables, means, SDs, medians, minimum and maximum, and absolute or relative frequencies will be reported.

Clinically significant decisional conflict will be calculated and defined by a score of ≥25/100 on the Decision Conflict Scale, which is the most commonly used threshold to distinguish a harmful level of decisional conflict [62-64].

We will compare primary and exploratory outcome measures between the 2 patient groups (baseline and intervention) using Student *t* tests or analysis of variance. Parametric or nonparametric statistics (depending on the distribution of the data) will be used for the analysis of the patient groups from the baseline and intervention phases.

We will compare clinical confounders (time of integration of specialized palliative services into care; aggressiveness of therapy [anticancer treatment <14 days before death and place of death]) between the 2 patient groups (baseline and intervention) by comparing mean values. Measures of variability (SD) will be calculated.

Given the practice-based character and the small sample size of the study, we refrain from extensive measurement and multivariate analysis of mediators and moderators of the intervention effects. For the latter reason, we do not plan to use multiple imputation of missing values. Missing values will be handled by allowing a maximum of 35% missing in the calculation of scale scores.

*P* values of the corresponding statistical tests comparing treatment groups (ie, 2-sample *t* tests for continuous variables and chi-square tests for categorical data) will be given. Statistical significance will be assessed at the level of α=.05 (two-sided).

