### Study Setting

The study is bicentric and will be carried out at the Department of Medical Oncology, National Center for Tumor Diseases (NCT), Heidelberg University Hospital, Heidelberg, Germany and at the Department of Internal Medicine II (Palliative Care), University of Jena, Jena Germany. Patients will be recruited in Heidelberg (oncology) and Jena (specialized palliative care). This study was approved by the Ethics Committee of the Medical Faculty of the University of Heidelberg and University of Jena.

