### Design and Settings

First, patients will be recruited in a baseline phase lasting 4 months to observe usual care without using the DA. It means that oncologists will inform patients about further treatment options for cancer-specific therapy, side effects, and potential benefit, but they will not explicitly address that best supportive care would also be an option and will not use a decision support tool for eliciting patient preferences and assisting in decision making. The baseline phase will be followed by an intervention phase lasting 6 months. Oncologists and patients will use the DA in the same situation (change of treatment needs to be discussed with the patient because of disease progression, treatment toxicity, or other reasons). A minimum of 40 doctor-patient encounters will be included in the 4-month baseline, and 40 doctor-patient encounters will also be included in the 6-month DA intervention phase. The whole sample will encompass 80 doctor-patient encounters. The planned sample size is largely determined by the feasibility of recruiting patients within the available project duration.

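### The primary comparison of two sequential, non-randomised groups adjusts for neither site nor any pre-consultation score, so it is open to case-mix bias and may be less precise than it need be

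*Protocol article*

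**What the plan says.** The primary outcome is decisional conflict: "Level of decisional conflict will be measured with the Decision Conflict Scale" (Measurements, pre-post study).

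Design and Settings describes two consecutive phases: "First, patients will be recruited in a baseline phase lasting 4 months to observe usual care without using the DA". A 6-month phase with the decision aid follows. Each phase has 40 doctor-patient encounters, 80 in all; the Abstract gives 70. The size is attributed to feasibility. Study Setting adds: "Patients will be recruited in Heidelberg (oncology) and Jena (specialized palliative care").

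On the analysis, Data Analysis says "We will compare primary and exploratory outcome measures between the 2 patient groups (baseline and intervention) using Student" t tests or analysis of variance. It then says "Parametric or nonparametric statistics (depending on the distribution of the data) will be used", and that P values come from "2-sample *t* tests for continuous variables and chi-square tests for categorical data". The threshold is fixed: "Statistical significance will be assessed at the level of α=.05 (two-sided"). No covariate is named. The section declines multivariate analysis of mediators and moderators because the study is practice-based and small.

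On timing, Measurements says: "The questionnaires will be completed by patients and oncologists before and after the intervention".

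**The concern.** Patients in the two phases differ in calendar period and may differ in site, tumour type, care setting and starting level of conflict. Nothing in the design balances these. In an unadjusted two-sample test, any such difference that is related to the Decisional Conflict Scale score becomes part of the apparent effect of the decision aid.

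The safeguards in the text do not close this gap:

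- Two-site recruitment and a trained study nurse (Sample Characteristics) do not equalise the site mix between phases.
- The clinical confounders in Data Analysis are only compared between groups. Treatment close to death and place of death arise after the consultation, and the Conceptional Framework section says the aid may reduce intensive treatment. They are potential outcomes and cannot serve as case-mix adjusters.
- Declining to model mediators and moderators is a different matter from adjusting for confounders or a starting score.

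The choice between a parametric and a rank test is also left until the distribution has been seen, so the effect measure of the primary analysis is not fixed. At stake is the estimate that the pilot is meant to hand on to the sizing of a definitive trial.

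**Working it through.** The article states no power calculation (no effect size, SD or power), so there is none to reproduce. The group sizes agree within Design and Settings: 40 + 40 = 80.

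**Inputs from the article:** 40 per phase (35 if the Abstract's 70 is split equally); two-sided α = 0.05; unadjusted two-sample test; two sites.

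**Inputs assumed, because the article gives none:** one encounter per patient; 80% power; size of case-mix shift; site difference; pre-post correlation r.

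**1. Effect of a case-mix shift on the error rate.** For a shift of b SD and no effect of the aid, SE = √(2/n), and the rejection probability is Φ(b/SE − 1.96) + Φ(−b/SE − 1.96). With n = 40, SE = √(2/40) = 0.224.

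| Shift b (SD) | 40 per phase | 35 per phase |
|---|---|---|
| 0.1 | 7.3% | 7.0% |
| 0.2 | 14.5% | 13.3% |
| 0.3 | 26.9% | 24.1% |

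**2. How such a shift could arise.**
- Site mix: bias = change in site share × site difference. Share changes of 0.1 to 0.3 and site differences of 0.3 to 0.8 SD give 0.1 × 0.3 = 0.03 SD up to 0.3 × 0.8 = 0.24 SD. In scale points, a 10-point site difference and a Jena share moving from 20% to 40% give 10 × (0.40 − 0.20) = 2 points.
- Starting score: bias = r × imbalance. With r = 0.5 and an imbalance of 0.4 SD, this is 0.5 × 0.4 = 0.2 SD.

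**3. Precision, only if a pre-consultation score exists in both phases.** The unadjusted detectable difference at 40 per phase is (1.960 + 0.842) × √(2/40) = 0.626 SD by the normal approximation, and 0.634 SD by the t distribution. Adjusting for the pre-score multiplies it by √(1 − r²). The equivalent unadjusted group size is 40/(1 − r²).

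| r (assumed) | Factor | Detectable difference (0.634 × factor) | Equivalent n per phase |
|---|---|---|---|
| 0.3 | 0.954 | 0.605 SD | 44 |
| 0.5 | 0.866 | 0.549 SD | 53 |
| 0.7 | 0.714 | 0.453 SD | 78 |

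At 35 per phase (normal approximation), 0.670 SD becomes 0.639, 0.580 or 0.478 SD. The factor ignores the small loss of precision that arises when the covariates themselves differ between phases.

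**The case against.** The strongest objection is that a paired pre-score is not established. Measurements does not say which instruments are completed before, or what that word means in the usual-care phase, which has no intervention. The pre-post study section describes the baseline and intervention phases as the two measurement phases, so the sentence could mean one set of questionnaires per patient. The scale also covers satisfaction with the choice, which is hard to rate before choosing. This objection stands. A pre-score in both phases is the natural reading, but a reader who infers that paid-for precision is certainly being discarded goes further than the text. The adjustment for site does not depend on it.

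A reader might also infer that the result is biased. The article supports only that it is open to bias. All the shifts above are assumptions, and the Discussion says testing is mainly in Heidelberg, so a Jena share of 40% may be high. One set of eligibility criteria applies to both sites.

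A further objection is that adjustment may be left to an analysis plan that is not shown, and that analysis of variance could carry site as a factor. It is true that the article does not exclude adjustment. However, it does fix the groups, the test and the threshold, and it names no factor other than phase.

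Finally, this is a pilot that sets out to explore potential effects, and the Discussion acknowledges the small sample. That lowers the stakes. It does not remove the point, because a primary outcome is still tested at 0.05 and its effect is linked to the sample size of a definitive trial.

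**Conclusion.** The point holds in limited form. As stated, the primary analysis is an unadjusted comparison of different patients in consecutive, non-randomised phases across two care settings. It is open to case-mix bias whose size and direction cannot be known in advance; modest assumed shifts of 0.1 to 0.3 SD would take the nominal 5% error rate to roughly 7% to 27%. Adjusting for site is feasible with either 70 or 80 patients, and nothing in the text rules it out.

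The gain in precision (from about 0.63 to about 0.61, 0.55 or 0.45 SD at 40 per phase) is conditional on a pre-consultation Decisional Conflict Scale score in both phases and on the assumed correlations. Adjustment removes only measured imbalance. Calendar time stays confounded with phase under any analysis of this design. The change should be made, but the pilot setting does not make it critical.

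**What to change.** 1. State in Measurements which instruments are completed before the consultation, and whether this applies in both phases.
2. Make the primary analysis a linear model of the post-consultation Decisional Conflict Scale score on phase and site, adding the pre-consultation score if step 1 confirms that it exists in both phases. If it does not, adjust for site and for characteristics already known at recruitment, such as tumour type or inpatient/outpatient setting, without adding questionnaires. Do not adjust for measures that arise after the consultation.
3. Report the adjusted difference with a 95% confidence interval.
4. Keep the t test or a rank test as a named sensitivity analysis, and remove the choice of primary test from the observed distribution.
5. Describe the result as an adjusted before-after difference in which calendar time remains confounded with phase, and not as a demonstrated effect of the aid.

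**Cost:** mainly wording, plus the clarification in step 1; a few degrees of freedom; and a stated rule for missing pre-scores. No new data collection is needed if the fallback in step 2 is used where no pre-score exists.
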